#### 658 **6.8.6 Procedure of Reporting Serious Adverse Events**

659 All SAEs have to be reported, whether or not considered causally related to the treatment, or  
660 to the study procedure(s).

For fatal or life-threatening AEs where important or relevant information is missing, active follow-up is undertaken immediately. Investigators or other site personnel inform representatives of the local institutional review board of any follow-up information on a previously reported SAE immediately, or no later than 24 hours of when he or she becomes aware of it.

## **7. RESTRICTIONS DURING THE STUDY AND CONCOMITANT TREATMENTS**

The following restrictions apply while the patient is receiving study treatment and for the specified times before and after:

### **Female patient of child-bearing potential:**

- Female patients of childbearing potential who are not abstinent and intend to be sexually active with a non-sterilized male partner must use at least 1 highly effective method of contraception (Table 1) from the time of screening throughout the total duration of the study. Non-sterilised male partners of a female patient of childbearing potential must use male condom plus spermicide throughout this period. Cessation of birth control after this point should be discussed with a responsible physician. Periodic abstinence, the rhythm method, and the withdrawal method are not acceptable methods of birth control. Female patients should also refrain from breastfeeding throughout this period.

### **Male patients with a female partner of childbearing potential:**

- Non-sterilized male patients who are not abstinent and intend to be sexually active with a female partner of childbearing potential must use a male condom plus spermicide from the time of screening throughout the total duration of the study. However, periodic abstinence, the rhythm method, and the withdrawal method are not acceptable methods of contraception. Male patients should refrain from sperm donation throughout this period.
- Female partners (of childbearing potential) of male patients must also use a highly effective method of contraception throughout this period (Table 1).

N.B Females of childbearing potential are defined as those who are not surgically sterile (ie, bilateral salpingectomy, bilateral oophorectomy, or complete hysterectomy) or post-menopausal.

Women will be considered post-menopausal if they have been amenorrheic for 12 months without an alternative medical cause. The following age-specific requirements apply:

• Women < 50 years of age would be considered post-menopausal if they have been amenorrheic for 12 months or more following cessation of exogenous hormonal treatments and if they have luteinizing hormone and follicle-stimulating hormone levels in the post-menopausal range for the institution.

• Women  $\geq$  50 years of age would be considered post-menopausal if they have been amenorrheic for 12 months or more following cessation of all exogenous hormonal treatments, had radiation-induced menopause with last menses > 1 year ago, had chemotherapy-induced menopause with last menses > 1 year ago.

Highly effective methods of contraception, defined as one that results in a low failure rate (ie, less than 1% per year) when used consistently and correctly are described in Table 1. Note that some contraception methods are not considered highly effective (e.g. male or female condom with or without spermicide; female cap, diaphragm, or sponge with or without spermicide; non-copper containing intrauterine device; progestogen-only oral hormonal contraceptive pills where inhibition of ovulation is not the primary mode of action [excluding Cerazette/desogestrel which is considered highly effective]; and triphasic combined oral contraceptive pills).

**Table 1. Highly Effective Methods of Contraception (<1% Failure Rate)**

| Barrier/Intrauterine methods                                                                                                                                     | Hormonal Methods                                                                                                                                                                                                                                                                                                                                                                                                                                                                                                                                                                                                                     |
|------------------------------------------------------------------------------------------------------------------------------------------------------------------|--------------------------------------------------------------------------------------------------------------------------------------------------------------------------------------------------------------------------------------------------------------------------------------------------------------------------------------------------------------------------------------------------------------------------------------------------------------------------------------------------------------------------------------------------------------------------------------------------------------------------------------|
| 
 
Copper T intrauterine device
 
Levonorgestrel-releasing intrauterine system (e.g., Mirena®)a
 
 | 
 
Implants: Etonogestrel-releasing implants: e.g. Implanon® or Norplant®
 
Intravaginal: Ethinylestradiol/etonogestrel-releasing intravaginal devices: e.g. NuvaRing®
 
Injection: Medroxyprogesterone injection: e.g. Depo-Provera®
 
Combined Pill: Normal and low dose combined oral contraceptive pill
 
Patch: Norelgestromin/ethinylestradiol-releasing transdermal system: e.g. Ortho Evra®
 
Minipill: Progesterone based oral contraceptive pill using desogestrel: Cerazette® is currently the only highly effective progesterone-based
 
 |

## 8. STATISTICAL PLAN

The sample size for this phase 2 study is based on the following assumptions:

The primary endpoint is progression-free survival.

The following hypotheses are used:

- $p_0=60\%$ , assumed objective response after TACE or RFA as bridging therapy
- $p_1=85\%$ , expected objective response after SBRT as bridging therapy

With a two-sided alpha value of 0.05 and an 80% power of detection of statistical significance, 28 patients were required. Assuming a dropout rate of about 20%, 35 patients were required for eligibility screening in this study.

Kaplan-Meier methods are used for survival analysis. Log-rank tests are performed for comparison of survival among different patient subgroups. Cox regression with univariable and multivariable analyses are performed for prognostic factors PFS and OS.

All statistical analyses are performed by Statistical Package for Social Sciences (SPSS) version 24, or R 3.6.1 or more advanced versions. Statistical significance is defined as  $P$  value  $< .05$  (two-sided).

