|                           | 
fluorodeoxyglucose (FDG) and 11C-acetate (ACC) was proven to be more sensitive and specific to FDG-alone PET-CT scan in HCC diagnosis and staging. On the other hand, magnetic resonance imaging (MRI) with gadoxetate disodium is more accurate and sensitive to gadolinium-enhanced MRI and contrast-enhanced CT scan in detecting HCC and differentiate it from other non-HCC causes.
 
Based on the above, we are carrying out a phase 2 single-arm study on using SBRT as a bridging therapy before liver transplantation for HCC patients within LT criteria, monitored by pretreatment and posttreatment dual-tracer PET-CT scan and MRI scan with gadoxetate disodium.
                                                                                                                                                                                                                                                                                                                                                                                                                                                                                                                                                         |
| Study Design       | 
This study is a prospective phase 2, single arm study assessing the efficacy and safety of SBRT as bridging therapy in patients with HCC before LT, monitored by regular pretreatment and posttreatment dual-tracer PET-CT scan.
 
Radical radiotherapy will be delivered by stereotactic body radiation therapy (SBRT) with 35 to 50Gy in 5 fractions over 5 to 14 days.
 
Patient is mandatory to have histologically or radiologically confirmed HCC.
 
The co-primary endpoints of this study will be progression-free survival, and objective response. Patients will undergo tumor assessment with dual-tracer PET-CT scan and MRI scan with gadoxetate disodium at baseline, and then at 3 months and 6 months after SBRT and continuous interval dual-phase contrast CT scans every 3 months after SBRT for treatment response evaluation and surveillance by mRECIST, RECIST 1.1 and irRECIST until LT is done or when progressive disease develops.
 
Safety assessments will include the incidence, nature, and severity of adverse events, changes in vital signs and laboratory abnormalities grade per National Cancer Institute Common Terminology Criteria for Adverse Events (NCI CTCAE), Version 4.0.
 |

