|                                          |                                                                                                                                                                                                                                                                                                                                                                                                                                                                                                                                             |
|------------------------------------------|---------------------------------------------------------------------------------------------------------------------------------------------------------------------------------------------------------------------------------------------------------------------------------------------------------------------------------------------------------------------------------------------------------------------------------------------------------------------------------------------------------------------------------------------|
|                                          | 
Kaplan-Meier methods are used for survival analysis. Log-rank tests are performed for comparison of survival among different patient subgroups. Cox-regression with univariable and multivariable analyses are performed for prognostic factors of all prespecified study endpoints.
 
All statistical analyses are performed by Statistical Package for Social Sciences (SPSS) version 24 or R 3.6.1 or more advanced versions. Statistical significance is defined as <math>P</math> value <math>< .05</math> (two-sided).
 |
| Duration of Patient Participation | The duration of treatment depends on the availability of LT after SBRT, typically ranging from 6 months to 4 years.                                                                                                                                                                                                                                                                                                                                                                                                                         |

3

4

5

6

7

8

9

10

11

12

13

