## **8.1 Analysis Endpoints**

### **8.1.1 Efficacy Endpoint**

#### **Primary**

- Progression-free survival (PFS)
  - PFS is calculated from the start of SBRT to the date of radiologically confirmed progressive disease based on RECIST 1.1, mRECIST, and PERCIST, or death from any cause
- Best objective response as defined by RECIST 1.1, mRECIST, and PERCIST

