**APPENDIX 2. Scanning algorithm of magnetic resonance imaging (MRI) scan with gadoxetate disodium injection**

MRI scanning was conducted with a 3-Tesla MR scanner (Philips Achieva 3.0T TX, Philips Medical Systems, Best, The Netherlands) throughout the whole study as shown below. The same scanner is used for all scans for all patients recruited into this study. MRI scans were performed at baseline, then at every 3 months until liver transplantation was performed or progressive disease was observed, whichever came earlier. All HCC lesions were evaluated by two independent radiologists and any discrepancy in determining the nature of the lesions was solved by consensus.

(1) T2-weighted TSE single-shot in 5mm section thickness

(2) Breath-hold triggered T1-weighted in-phase and opposed sequences in 7mm section thickness

(3) T2-weighted SPAIR with TE 80 and 160 in 7mm section thickness

(4) Diffusion-weighted single-shot echo planar imaging with respiratory triggering

(5) Gadoxetate disodium (0.025mmol/kg body weight)-enhanced dynamic phases: unenhanced, late arterial-phase, portal-venous phase, and delayed phases with T1-weighted three-dimensional (3D) turbo-field-echo sequence (T1 high-resolution isotropic volume examination, THRIVE) with a 2-mm section thickness and a FOV of 32-38 cm.

1038

1039 **APPENDIX 3. Positron-emission tomography with integrated contrast-enhanced computed**  
1040 **tomography (PET-CT) with two radiotracers (C-acetate [ACC] and F-**  
1041 **fluorodeoxyglucose [FDG])**

1042 Dual Tracer PET-CT scan was performed at baseline, and then every 3 months after SBRT  
1043 until liver transplantation done or until progressive disease whichever came earlier. All scans  
1044 were performed using the same scanner and protocol (Discovery VCT, 64-MDCT; GE  
1045 Healthcare Bio-Sciences Corp., Piscataway, New Jersey, USA). All patients are required to fast  
1046 for  $\geq 6$  hours, and the blood glucose concentration is  $\leq 8$  mmol/L before radiopharmaceutical  
1047 injection. ACC (440–590 MBq; 8.0 MBq/kg of body weight) was then administered  
1048 intravenously, and limited upper abdomen coverage acquired at 1 minute followed by a whole  
1049 body imaging is performed at 11 minutes after injection. Data acquisition with an integrated in-  
1050 line PET-CT scanner (Discovery VCT, 64-multislice CT; GE Healthcare Bio-Sciences Corp, NJ)  

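### PFS is to be estimated by Kaplan-Meier alone, although scheduled imaging ends at transplant and the protocol does not say how transplant enters PFS

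*Protocol*

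**What the plan says.** PFS is a primary endpoint in the synopsis, in Section 2.1 and in Section 8.1.1, where "PFS is calculated from the start of SBRT to the date of radiologically confirmed progressive disease" on the named response criteria, or to death from any cause. Transplant is not listed as an event, a competing event or a reason for censoring.

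On analysis, Section 8 states "Kaplan-Meier methods are used for survival analysis", with log-rank tests for subgroups and Cox regression for prognostic factors. The synopsis says much the same in its row on the statistical analysis plan. Neither names a cumulative-incidence method.

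On imaging, the synopsis continues tumour assessment "until LT is done or when progressive disease develops". Appendix 2 schedules MRI "until liver transplantation was performed or progressive disease was observed, whichever came earlier". Appendix 3 schedules dual-tracer PET-CT "until liver transplantation done or until progressive disease whichever came earlier". Section 1.1.5 says the same in substance. Section 6.5 sets three-monthly imaging without repeating the stop at transplant.

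On the role of transplant, Section 1.3.1 expects the treatment to give patients enough time to wait for a graft. The synopsis adds: "The duration of treatment depends on the availability of LT after SBRT, typically ranging from 6 months to 4 years".

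**The concern.** In this population transplant is the hoped-for outcome, and it also ends the scheduled search for progression. It is therefore not ordinary loss to follow-up. Kaplan-Meier has only two places to put a transplanted patient:

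- **Censored at transplant.** The curve then describes progression or death in a setting where no transplant takes place, and does so without bias only if censoring is independent of prognosis. It does not give the proportion who progress or die while waiting.
- **Kept at risk after transplant.** This is the literal reading of death from any cause. Deaths after the graft count, but progression is no longer looked for on schedule, so as an estimate of PFS the curve is too favourable.

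At stake is how a primary endpoint is read. The synopsis gives reduction of waiting-list dropout, quoted at 10% to 40%, among the aims of bridging therapy. A reader is likely to take the PFS curve as the risk run while waiting, and under either handling it is not that.

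**Working it through.** **The plan's own figure.** The only computed figure is the sample size, which rests on objective response (60% against 85%, two-sided alpha 0.05, power 80%). A one-sample normal approximation gives [1.960 × √(0.60 × 0.40) + 0.842 × √(0.85 × 0.15)]² / 0.25² = 25.4, so 26; with continuity correction it is 29.3, so 30. The stated 28 lies between them, and 28 / (1 − 0.20) = 35. None of this uses PFS, so the present point leaves it alone.

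**Inputs for the illustration.** The documents give no hazard for progression, death or transplant. The following are assumptions: constant, independent monthly hazards, *a* = 0.01 to 0.03 for progression or death and *b* = 0.02 to 0.08 for transplant, with *t* = 24 months.

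**Formulas.**

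- One minus Kaplan-Meier, censoring at transplant: 1 − exp(−*a t*).
- Actual proportion with progression or death before transplant: *a*/(*a*+*b*) × [1 − exp(−(*a*+*b*)*t*)].
- Proportion transplanted first: *b*/(*a*+*b*) × [1 − exp(−(*a*+*b*)*t*)].

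**Middle case, *a* = 0.02, *b* = 0.05.** One minus Kaplan-Meier is 1 − exp(−0.48) = 38.1%. The actual pre-transplant risk is (0.02/0.07) × [1 − exp(−1.68)] = 23.2%. The proportion transplanted is (0.05/0.07) × [1 − exp(−1.68)] = 58.1%.

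**Paired comparison over the assumed range, 24 months.**

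| *a* | *b* | 1 − Kaplan-Meier | Actual risk before transplant | Excess (points) |
|---|---|---|---|---|
| 0.01 | 0.02 | 21.3% | 17.1% | 4 |
| 0.01 | 0.08 | 21.3% | 9.8% | 12 |
| 0.02 | 0.02 | 38.1% | 30.9% | 7 |
| 0.02 | 0.05 | 38.1% | 23.2% | 15 |
| 0.02 | 0.08 | 38.1% | 18.2% | 20 |
| 0.03 | 0.02 | 51.3% | 41.9% | 9 |
| 0.03 | 0.08 | 51.3% | 25.3% | 26 |

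The Kaplan-Meier column does not move with *b*; the actual-risk column does.

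**Second set of assumptions.** With a 12-month event risk of 20% and a median wait of 12 months, one minus Kaplan-Meier against actual risk is 20.0% against 14.6% at 12 months and 36.0% against 20.5% at 24 months. A simulation with 28 patients per trial gave mean 24-month values of 36.0% and 20.5%. Over event risks of 10–40% and median waits of 6–48 months the 24-month excess ran from 3 to 38 points and was never negative.

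**If patients stay at risk after transplant.** The curve then counts events before transplant plus deaths after it, and misses progression after the graft unless an unscheduled scan finds it. Its error as an estimate of PFS is in the favourable direction. The documents give nothing from which to size it.

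**The case against.** The strongest reply is that this is a choice of estimand and not a mistake in Kaplan-Meier. Tumour control after radiotherapy as if transplant had not intervened is a legitimate question; no listed objective asks for waiting-list dropout or the transplant rate; and a detailed censoring rule may sit in a statistical analysis plan that is not shown. PFS also has no stated null or threshold, so the curve is descriptive and no go/no-go decision turns on it.

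Much of that stands. The censored curve is valid for the question it answers, and the protocol nowhere writes that patients are censored at transplant. It does not dispose of the point, because the protocol fixes the estimator itself, for a primary endpoint, while stopping imaging at the event that the treatment is meant to reach.

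Three stronger inferences are tempting and are not supported:

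- **That Kaplan-Meier results would not be comparable between centres.** In the model above it is the reverse: one minus Kaplan-Meier stays at 38.1% when *a* = 0.02, while the actual risk falls from 30.9% to 18.2% as *b* rises from 0.02 to 0.08.
- **That censoring is shown to be informative because a patient who progresses may lose eligibility.** Progression is already the PFS event, so what follows it cannot make earlier censoring informative. Prognosis before progression would have to predict transplant. That is plausible, but the documents do not show it.
- **That deaths after transplant should be removed from PFS.** This would redefine a co-primary endpoint, and the problem can be met without it.

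**Conclusion.** The point holds in a limited form. Kaplan-Meier is the only estimator fixed for PFS, scheduled imaging ends at transplant, and the handling of transplant is not stated. Neither available handling yields the proportion who progress or die before a graft.

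A reader might infer that the planned PFS analysis overstates risk outright. That follows only if patients are censored at transplant, and only against the actual risk while waiting. On those two conditions the direction is certain. The size, about 4 to 26 points at 24 months, rests wholly on assumed constant, independent hazards; at the low end it is small for 28 patients.

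**What to change.** In Section 8, and in the matching synopsis row:

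1. State that the Kaplan-Meier estimate of PFS is censored at transplant and is to be read as risk in the absence of transplant.
2. Beside it, report the Aalen-Johansen cumulative incidence of progression or death before transplant, with transplant as a competing event, and the cumulative incidence of transplant.
3. State that Cox models for PFS are interpreted as cause-specific.

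The cost is a few lines of text and one further analysis. R is already among the named packages, and the transplant date is needed anyway to end imaging. The small downside is that the cumulative incidence depends on the local transplant rate, which is why both estimates should be shown. No patient procedure changes.

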## **8.1 Analysis Endpoints**

### **8.1.1 Efficacy Endpoint**

#### **Primary**

- Progression-free survival (PFS)
  - PFS is calculated from the start of SBRT to the date of radiologically confirmed progressive disease based on RECIST 1.1, mRECIST, and PERCIST, or death from any cause
- Best objective response as defined by RECIST 1.1, mRECIST, and PERCIST

#### **Secondary**

- Local control rate as defined by RECIST 1.1, mRECIST, and PERCIST
- Local control rate
- Overall survival (OS)
  - Calculated from start of SBRT to the date of death from any cause

### **8.1.2 Safety Endpoint**

- Toxicity profiles as determined by Common Terminology Criteria for Adverse Events (CTCAE) version 4.0

### **8.1.3 Exploratory**

- Prognostic factors of PFS and OS
- Predictive factors of objective response after SBRT

- Change in Child-Pugh scores before and after SBRT, especially the incidence of increase in Child-Pugh score by  $\geq 2$  points after SBRT

## **9. ETHICAL, REGULATORY & STUDY OVERSIGHT CONSIDERATIONS**

### **9.1 Ethical Conduct of the Study**

The study will be performed in accordance with ethical principles that have their origin in the Declaration of Helsinki and are consistent with ICH/Good Clinical Practice, and applicable regulatory requirements patient data protection.

